Most pesticides are synthetically-produced organic and inorganic chemical compounds, although biological agents are also coming into wider use [25]. The most commonly imported pesticides are organophosphates (OPPs) and carbamates [26]. OPPs and carbamates kill insects by blocking acetylcholinesterase (AChE), an enzyme that catalyses hydrolysis of a neurotransmitter acetylcholine, resulting in overstimulation of the neuromuscular system and the parasympathetic nervous system. Exposure to OPPs by inhalation or ingestion with or without food is toxic to the human body. It can be detected by a reduced AChE concentration in capillary blood. Acute OPP poisoning symptoms include: increased salivation, diarrhoea, vomiting, muscle tremors, gastrointestinal upset, and confusion [27]. The onset of symptoms can start within minutes or hours and last for days to weeks. In the long term, lower-dose exposure to OPPs has been reported to cause polyneuropathy and cardiovascular diseases [28]. Carbamates can also pose both health and environmental hazard, including through groundwater contamination [29] and food [29,30].

The health impact of pesticide use has been a topic of heated debate for many years in Asian countries, both at national and local government levels. There is a need to prevent adverse health effects as part of a wider pesticides management strategy, and there would be major advantages in establishing a framework for cooperation within the Association of Southeast Asian Nations (ASEAN). At present, countries in the Mekong region have only their differing national strategies, and it would be valuable to compare approaches and develop a more uniform approach that takes the best ideas from each country.

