#### Measuring blood cholinesterase concentrations in agricultural workers

Exposure to pesticides can be detected by low acetyl cholinesterase enzyme (AChE) concentrations in capillary blood samples. To measure AChE, we will utilise field kits containing lancets and reactive paper test strips (AChE field test kits, lot U620164, manufactured by the Government Pharmaceutical Organisation [GPO] Thailand). Blood samples (0.2 mL/capillary) will be obtained from a lancet-punctured fingertip of participants, undertaken by volunteer assistants drawn from public health officers, nurses, paramedics, or doctors in the local area. The samples will be allowed to precipitate for 30–45 minutes, followed by the reactive paper test. After 7 minutes, changes in colour on a paper test strip will be recorded using the four categories specified on the standard instruction sheet provided by the GPO with the test kits. The categories are: normal (AChE units per ml >100); safe (87.5–99.9); at risk (75.0–87.4); and probable health impact (<75). The outcome of primary interest is probable health impact.

The blood test results will be analysed alongside the interview data to determine whether participants with AChE levels that indicate probable health impact differ in their agricultural practices, health knowledge, health-protective practices and extent of self-reported illness. We will use descriptive and inferential statistics to explore associations (if any) between key variables, in line with specialist advice on appropriate multivariate analyses.

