#### Reporting

The data for each country will be reported separately to inform national stakeholders and policy makers. If the data are sufficiently similar across countries, we shall consider a combined analysis in a multilevel model. Otherwise, we shall undertake a meta-analysis to accommodate high heterogeneity.

We believe that abnormal AChE levels anywhere within our estimated range (28%-42%) will suffice as triggers to modify behaviour. Our models will identify behaviours that might usefully be targeted.

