### Analysis outline

Data will be summarised using appropriate descriptive statistics; we will report on associations between agricultural methods, health knowledge, health-protective practices, self-reported illness and blood test results.

Data from each country will be analysed separately before considering whether an analysis of pooled data is appropriate.

Description of all variables: frequencies, or ranges and measures of central tendencyCombining structured interview responses to give overall measures of: outcomes, knowledge, practices/behaviours and exposures. The variables to be combined will be listed *a priori*.Measures of ill-health, knowledge, behaviours and exposures will be described separately and together.Bivariate explorations will be used to examine the variables shown in Table 1.

**Table 1 pone.0258134.t001:** Contingency tables for each comparison.

	Ill-health measures	Exposure	Practices/behaviours	Knowledge	Cholinesterase concentration
Ill-health measures					
Exposure					
Practices/behaviour					
Knowledge					
Cholinesterase concentration					

4. Multivariate analysesPrimary outcomes: AChE concentrations, ill-health measures, separately & togetherCovariates to be tested one by oneCovariates with P<0.20 will be entered into exploratory models

a) Logistic regression: high AChE concentration, any ill-health, each health issue (modelling strategy to be based on backwards LR, -2LL, VIF, check enter model)

Predictors:

1. Behaviours
a. Likely to increase exposureb. Likely to decrease exposure2. Knowledge score3. Cholinesterase concentrations (when exploring ill-health)4. Significant covariates from one-by-one testing will include: location, SES, education, literacy (ability to write), age, gender, hours worked, distance between home and farm.

Sensitivity analyses will, in turn, exclude:

Migrant workersEarlier diagnosis of pesticide poisoning

A priori sub-group analyses:

Each countrySelf-employedLowest SES or income categoryNo formal education

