### Limitations

Because this study is a development project, it must be conducted with modest resources and a tight time schedule. This limits the scale and generalisability of the study. Other operational considerations include the need to proceed against the background of the COVID-19 pandemic, so that we must restrict data collection to accessible districts in a single province in each country. This means that we cannot use probability sampling for all levels of site and respondent selection, and affects the levels of statistical significance assumed in our analysis. As with all non-randomised studies, we cannot assume that association equates to causation. Rather, our aim is to identify behaviours predictive of adverse outcomes, and suggest strategies to target these behaviours.

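### The ill-health models adjust behaviour effects for AChE, which lies between behaviour and illness, so their behaviour odds ratios tend to understate the total effect on illness

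*Protocol article*

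**What the plan says.** Under Multivariate analyses, the Analysis outline names AChE and the ill-health measures as primary outcomes. The models are given as "Logistic regression: high AChE concentration, any ill-health, each health issue". One predictor list serves them all: behaviours (split by whether they are expected to raise or lower exposure), knowledge score, "Cholinesterase concentrations (when exploring ill-health", and covariates retained after one-by-one testing. Selection is described as "modelling strategy to be based on backwards LR, -2LL, VIF, check enter model". The outline describes no multivariable ill-health model that omits AChE, and no mediation analysis.

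On the role of AChE, the section on measuring blood cholinesterase states: "Exposure to pesticides can be detected by low acetyl cholinesterase enzyme (AChE) concentrations in capillary blood samples". The Background gives AChE inhibition as the toxic mechanism of organophosphates and carbamates, "resulting in overstimulation of the neuromuscular system and the parasympathetic nervous system", and then lists the symptoms of poisoning.

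On the use of the models, the Reporting section says "Our models will identify behaviours that might usefully be targeted". The Limitations section says "our aim is to identify behaviours predictive of adverse outcomes, and suggest strategies to target these behaviours", directly after warning that association is not causation.

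**The concern.** Taken together, these sections give a chain: behaviour changes exposure, exposure lowers AChE, and lowered AChE goes with symptoms. A model of illness that contains both behaviour and AChE compares workers who differ in behaviour but share the same AChE category. Whatever behaviour does to illness by changing AChE is removed from its coefficient. What remains is a direct effect, the part that bypasses measured AChE.

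Choosing behaviours to target in order to reduce illness needs the total effect. If the AChE-adjusted coefficients are used for that choice, behaviours that act mainly through organophosphate or carbamate exposure are ranked too low, and backward elimination may remove them from the model.

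**Working it through.** **The plan's own figure.** The design effect is 1 + (120 − 1) × 0.01 = 2.19. The interval is 0.35 ± 1.96 × √(2.19 × 0.35 × 0.65 / 360) = 0.35 ± 0.073, or 27.7% to 42.3%, which rounds to the stated 28% to 42%. The present point does not depend on this figure.

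**Inputs.** From the article: 360 respondents per country and 35% with abnormal AChE. Not in the article, so assumed: half of workers have the risky behaviour; illness is 23% in workers with normal AChE and without the behaviour (logit −1.2); ORs of 2 to 4 for behaviour→AChE and the same for AChE→illness; a direct behaviour→illness OR of 1 or 1.5; AChE misclassification of 0 to 20%. Clustering is ignored.

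**By hand: path ORs of 3, no direct effect, no error.**
- AChE: p0 + p1 = 0.70 and odds(p1) = 3 × odds(p0) give p0 = 0.229 and p1 = 0.471.
- Illness: 0.231 with normal AChE. Tripling the odds gives 0.475 with abnormal AChE.
- With the behaviour: 0.471 × 0.475 + 0.529 × 0.231 = 0.346.
- Without it: 0.229 × 0.475 + 0.771 × 0.231 = 0.287.
- Total OR = (0.346/0.654) / (0.287/0.713) = 1.31.
- Within each AChE category the OR is 1.00 by construction.

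**Other scenarios.** Large-sample behaviour ORs for illness, from logistic regressions simulated at n = 200,000:

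| Path ORs | Direct OR | AChE misclassified | Without AChE (total) | With AChE (as planned) |
|---|---|---|---|---|
| 2 | 1 | 0% | 1.12 | 1.00 |
| 3 | 1 | 0% | 1.31 | 0.99 |
| 4 | 1 | 0% | 1.52 | 1.00 |
| 3 | 1 | 10% | 1.32 | 1.12 |
| 3 | 1 | 20% | 1.32 | 1.21 |
| 4 | 1 | 20% | 1.52 | 1.34 |
| 3 | 1.5 | 0% | 1.92 | 1.51 |
| 3 | 1.5 | 20% | 1.92 | 1.78 |

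**At one country's sample size** (n = 360, 600 runs, path ORs of 3), adding AChE changes the behaviour OR and the share of runs with p < 0.05 as follows:
- Full mediation, no error: OR 1.34 to 1.02; share 26% to 4%, about the chance level.
- Full mediation, 20% misclassification: OR 1.33 to 1.22; share 25% to 16%.
- Added direct OR of 1.5, no error: OR 1.92 to 1.50; share 82% to 39%.

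In the runs with path ORs of 3, the separate regression of AChE on behaviour reached p < 0.05 in 80% to 100%. With path ORs of 2 and 20% misclassification, that share was 42%.

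**The case against.** The strongest reply is that the plan already finds these behaviours. The Reporting section ties the trigger for changing behaviour to abnormal AChE, the second objective concerns behaviours that predict high exposure, and the section on measuring cholinesterase names the lowest AChE category as the outcome of primary interest. AChE is itself regressed on behaviours, and in most of the scenarios above that model detects the behaviour far more often than any illness model does. Table 1 also crosses behaviours with ill-health without adjustment for AChE. All this stands, and it limits the harm. But ill-health is also listed as a primary outcome. The AChE model does not estimate an effect on illness, and the cross-tables do not adjust for age, location, socio-economic status or hours worked.

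The models are called exploratory and causal claims are disclaimed. That is fair, but the Limitations section goes on to strategies aimed at the behaviours found. The planned check of the enter model keeps every term, so elimination alone need not hide a behaviour; that model still contains AChE, however. The joint model has a proper use: for the AChE–illness association, behaviours are possible confounders and belong in it.

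A reader might infer two stronger claims, and the documents support neither:
- **That harmful behaviours will look harmless.** An OR near 1 needs the whole effect to pass through AChE and AChE to be measured without error. The article points the other way: a colour strip read in four categories, levels that begin to recover about three weeks after exposure, Thai results accepted if up to four weeks old, and interview items on herbicides and fungicides, for which no AChE mechanism is given.
- **That adjusting for behaviours blocks the knowledge effect in the same way.** Nowhere does the article say that knowledge acts through behaviour. It lists the two as parallel predictors.

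**Conclusion.** The point holds as a bias in the stated specification. The behaviour ORs in the planned ill-health models are direct effects conditional on measured AChE, not the total effects that targeting illness requires. They tend to understate the total effect, would remove it only under full mediation with accurate AChE, and may lead backward elimination to drop behaviours that matter.

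The size cannot be determined from the documents. Under the assumptions above, the loss runs from slight (1.92 to 1.78) to complete (1.31 to 0.99). The direction assumes no strong unmeasured common cause of AChE and illness; with one, adjusting for AChE could bias the behaviour ORs either way. The AChE model and the cross-tables soften the consequence without supplying an adjusted behaviour–illness effect.

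**What to change.** For any ill-health and for each health issue, fit the logistic model with behaviours, knowledge score and covariates but without AChE. Use this model for behaviour ORs on illness and for choosing what to target. Then add AChE in a second, separately labelled model, and use it for the AChE–illness association and the remaining direct behaviour effect. State that its behaviour ORs are not total effects. Run any backward elimination of behaviours in the first model, so that a behaviour is not dropped because AChE stands beside it.

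The cost is one extra model per ill-health outcome, with no change to sample, interview or blood testing.

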## Discussion

### Benefits of the study

The study will provide baseline knowledge on health impacts of pesticides use, as well as farm workers’ agricultural practices, health knowledge, health-protective behaviours and self-reported illnesses that will assist policy makers and healthcare planners in the three countries. The findings should help inform recommendations for health improvement, especially in the areas of workers’ self-care and safe work practices. Measuring the magnitude of the problem of pesticide exposure (as cholinesterase concentrations) in agricultural workers should provide valuable information on targeting and prioritisation for health workers responsible for local pesticides monitoring programmes. An assessment of similarities and differences between the three countries will be helpful in identifying best practice, and improving regulatory arrangements and monitoring systems.

More generally, this initial project will help develop cooperation and research capacity in the trans-national research network. In time it is hoped that the network can be developed further, so that funding can be obtained for follow-on projects on pesticides use and other health-related topics.

### Limitations

Because this study is a development project, it must be conducted with modest resources and a tight time schedule. This limits the scale and generalisability of the study. Other operational considerations include the need to proceed against the background of the COVID-19 pandemic, so that we must restrict data collection to accessible districts in a single province in each country. This means that we cannot use probability sampling for all levels of site and respondent selection, and affects the levels of statistical significance assumed in our analysis. As with all non-randomised studies, we cannot assume that association equates to causation. Rather, our aim is to identify behaviours predictive of adverse outcomes, and suggest strategies to target these behaviours.

### Risks

In the ongoing COVID-19 epidemic, there is a risk that recruitment targets will not be met. The safety of researchers is paramount, and it may be that data will have to be collected from villages and districts in close proximity to universities. This may render our sample unrepresentative of the national populations.

### Timeline

In accordance with the conditions of GCRF funding, expenditure for the fieldwork phase of this project needs to be incurred by October 15^th^ 2021. Data analysis and writing of a report and papers can continue later into 2021. Because the individual country teams are at different stages of the research process, it is not possible to specify a definitive timetable for all. However, in general terms the following will apply.

The structured interview instrument to be finalised by end of March 2021All REC applications to be submitted by end May 2021Collection of main background information and an outline review of relevant literature should be completed by end of May 2021.Study sites should have been identified and any necessary permission from local government officials or others to proceed obtained by end of July 2021.Fieldwork (interviews and blood tests) should have been completed by mid-October 2021.

At the time of writing, options for follow-on funding are being curtailed by the COVID-19 crisis. One consequence of the UK Government’s decision to reduce its overseas development aid budget from 0.7% to 0.5% of GDP is that many Global Challenge Research Fund calls have been suspended, and no funds will be allocated for internal disbursement by UK universities in 2021–22. The research team will endeavour to find other funding sources to take our network forward.
